**Positive affect**
Positive affect will be assessed by four items (cheerfulness, satisfaction, enthusiasm, and feeling relaxed) using 7-point Likert scales ranging from “not at all” (rating of 1) to “very much” (rating of 7)
**Aberrant salience**
The ecological momentary assessment measure comprises three items in line with [43]. The items will be rated on a 7-point Likert scale (ranging from 1 [“not at all”] to 7 [“very much”]): “Everything grabs my attention right now,” “Everything seems to have meaning right now,” and “I notice things that I haven’t noticed before”
**Self-esteem**
Three items will be rated on a 7-point Likert scale ranging from “not at all” (rating of 1) to “very much” (rating of 7): “I feel guilty,” “I doubt myself,” “I feel disappointed about myself”
**Self-compassion**
Three items will be rated on a 7-point Likert scale ranging from “not at all” (rating of 1) to “very much” (rating of 7): “I like myself,” “I feel safe,” “I feel benevolent”
**Psychotic experiences**
Psychotic experiences will be assessed using eight items on thought problems and hallucinations (“I see things that aren’t really there,” “I hear things that aren’t really there,” “I feel suspicious,” “It's hard to express my thoughts in words,” “I feel unreal,” “My thoughts are influenced by others,” “I can’t get these thoughts out of my head,” “I feel like I am losing control”) that will be rated on 7-point Likert scales ranging from “not at all” (rating of 1) to “very much” (rating of 7)
**Resilience**
If participants indicate that there was a negative event (valence −3 or −2), then the item “I had difficulties to recover” will be rated on a 7-point Likert scale
**Threat anticipation**
In line with previous research, we will ask participants to rate the likelihood of negative events happening to them in the future [43]. They will be asked to think of what might happen in the next few hours and to rate the item “I think that something unpleasant will happen” on a 7-point Likert scale from “not at all” (rating of 1) to “very much” (rating of 7)
**Disturbance**
“This prompt disturbed me” will be rated at the end of each assessment on a 7-point Likert scale from “not at all” (rating of 1) to “very much” (rating of 7)

### Clinical Feasibility, Acceptability, Treatment Adherence, and Intervention Fidelity

Clinical feasibility will be assessed in relation to the trial methodology and the delivery of the EMIcompass intervention to youth with early mental health problems. The feasibility of the trial methodology will be assessed based on the following criteria: (1) successful recruitment of at least 96 participants during the study period; (2) assessment of inclusion criteria in 95% of potential participants after obtaining written consent; (3) successful randomization of at least 92 participants after completion of eligibility and baseline assessment; and (4) a retention rate of at least 85% for assessment of outcomes at least at one of the two time points at postintervention and 4-week follow-up. In addition, the following criteria will be used for establishing the feasibility of delivering the EMIcompass intervention, including its acceptability, intervention adherence, and intervention fidelity: (1) satisfaction with the EMIcompass intervention in general, ease of use, accessibility and comprehensiveness of various components of the intervention in a debriefing questionnaire [30,90], and the subjective quality of EMIcompass using the mobile application rating scale [91]; (2) compliance with, and adherence to, the EMIcompass intervention protocol based on a satisfactory level of session attendance, an adherence checklist covering all core components [29,30,92], and adherence to EMI tasks (ie, mean number of consolidating/interactive EMI tasks completed per week); and (3) fidelity to the EMIcompass intervention protocol based on independent ratings of a random selection of audio recordings of three face-to-face sessions, including fidelity to session protocol (ie, independent rating of core components delivered by trained psychologist), ability to model and embody the spirit of compassion, and the use of microskills in compassion-focused therapy assessed by the Compassion Focused Therapy-Therapist Competence Rating Scale [93].

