The app will offer EMI tasks according to three types of delivery schemes: (1) enhancing, (2) consolidating, and (3) interactive EMI tasks that aim for ecological translation of therapeutic principles and techniques to daily life. Participants will be asked to complete one *enhancing task* per week, practicing new compassion-focused tasks such as self-compassionate writing, experiencing emotions as a wave, and discovering their own compassionate self. Furthermore, participants will be offered *consolidating tasks* covering components of *enhancing tasks* from previous days. The components of *consolidating tasks* will be extended each time an *enhancing task* has been presented until all components are covered. In addition, participants will be offered to complete a brief EMA of momentary stress, affective disturbance, and threat anticipation six times per day, 3 days per week. On the basis of these EMAs, *interactive* tasks will be offered if participants score high on momentary stress or negative affect. The threshold for triggering interactive tasks will be either high momentary negative affect operationalized as a score of 4 or higher (on a 7-point Likert scale ranging from 1-7) on items of established and validated EMA measures of negative affect (Textbox 2) or high momentary stress based on items of established and validated measures of EMA of event-related, activity-related, or social stress (ie, a score <0 on a bipolar scale ranging from −3 to 3).

Participants will be instructed in detail in the semantic meaning of the 7-point Likert and bipolar scales and encouraged to carefully observe moment-to-moment variation in, and make use of the full range when rating, these scales on EMA items that have been previously used and validated to measure moment-to-moment variation in stress or negative affect. Given that a crucial element of compassion-focused therapy is for individuals to use compassionate imagery in moments of high stress or negative affect, these interactive tasks reflect an important component of the EMIcompass intervention. Participants can decline the EMI tasks in each delivery scheme. After completing the intervention period, participants will return the study devices and will no longer have access to the app.

Ecological momentary assessment domains and measures.

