## Discussion

Transdiagnostic mechanisms implicated in the development of severe mental disorders are important targets for prevention and early intervention. Ecological translation of compassion-focused intervention components to individuals’ daily lives through an EMI offers new avenues for tangible prevention strategies delivering real-world and real-time interventions that are easily accessible by youth [36]. Findings from a recent, nationally representative survey suggest that psychological distress, social isolation, lack of company, and worrying during the COVID-19 pandemic were highly prevalent in youth and, interestingly, associated with the current use of and a positive attitude toward digital interventions [33]. EMIs are also amenable to enhancing access to mental health services for youth depending on their needs and preferences, for instance, by delivering low-threshold interventions by frontline mental health staff [116-118] as a component that can be rolled out across adolescent and adult mental health services and link in with what is urgently needed, that is, a wider youth mental health reform that aims to provide seamless coverage of mental health care with smooth transitions from adolescence to mature adulthood at an age of approximately 25 years [20]. Furthermore, EMIs allow for investigating the strength of the evidence in support of several causal criteria (ie, association, temporality, sole plausibility, and ecological validity) as part of the ecological interventionist causal model approach that targets candidate underlying psychological mechanisms in daily life to achieve sustainable change under real-world conditions [27]. However, robust, trial-based evidence on EMIs and other mHealth interventions remain very limited [26,27,29,36,116,119]. A key next step is to examine the efficacy of youth-friendly, accessible, interactive, real-time interventions targeting candidate mechanisms underlying the transdiagnostic phenotype of psychosis, mania, depression and anxiety and thereby, help preventing adverse outcomes later in life. While, in the current study, we use EMA items that have been previously used and validated to measure moment-to-moment variation in stress/negative affect, with considerable within-person variability having been observed for these items in several EMA studies [43,89,120], inter-individual differences in within-person variability as well as general response tendencies may influence the number of triggered EMI tasks and hence, further research is needed to optimize and personalize the assignment of EMI components, eg, by using methods of artificial intelligence, recurrent neural networks (RNNs) in particular [121]. For example, we currently aim to apply recurrent neural networks in an ongoing study of personalized digital mental health promotion and prevention in youth [33]. In addition, clinical staging models of severe mental disorders require further scrutiny, including heterogeneity in phenomenology, course, and outcome within individual stages [5,122,123].

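### EMI adherence is a raw count of completed tasks, but interactive tasks are offered only after a high negative affect or stress rating, so part of the count reflects symptoms and response style as well as compliance

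*Protocol article*

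**What the plan says.** In the protocol article, the section on clinical feasibility, acceptability, treatment adherence and intervention fidelity states that "the following criteria will be used for establishing the feasibility of delivering the EMIcompass intervention". The second of these criteria, compliance and adherence, has three parts: session attendance, an adherence checklist, and "adherence to EMI tasks (ie, mean number of consolidating/interactive EMI tasks completed per week".

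The section on the experimental condition sets out how tasks reach the participant:

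- Enhancing tasks: one is requested per week.
- Consolidating tasks: "Furthermore, participants will be offered *consolidating tasks* covering components of *enhancing tasks* from previous days". No symptom trigger is attached and no weekly number is given.
- Interactive tasks: these "tasks will be offered if participants score high on momentary stress or negative affect". The trigger is negative affect at "a score of 4 or higher (on a 7-point Likert scale ranging from 1-7") or stress at "a score <0 on a bipolar scale ranging from −3 to 3". The brief EMAs that can set it off are offered "six times per day, 3 days per week".

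Tasks of every type may be declined. The Discussion accepts that differences in within-person variability and response tendencies "may influence the number of triggered EMI tasks", but does not connect this to the adherence measure. The Statistical Analysis section says that feasibility will be graded green, yellow or red, with further detail in the SAP.

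**The concern.** Adherence should describe what a participant does with the tasks offered. A count of completed tasks equals the number offered multiplied by the share taken up. For interactive tasks, the number offered is set by the participant's own ratings of affect and stress. Two participants with the same willingness can therefore have different counts. A group whose negative affect or stress declines over the 6 weeks would be expected to show a falling count with no change in compliance.

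Feasibility is the first aim of the trial and part of its stated primary objective, and the results are meant to inform a definitive trial. A low count could mean that participants refused tasks, that they ignored the EMA prompts, or that they were seldom distressed enough to trigger a task. These explanations call for different changes to the intervention or the trial, and the count alone cannot tell them apart.

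**Working it through.** The article gives no figure for expected adherence, so there is nothing to reproduce. The check is a direct expectation.

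**Input from the document:** 6 EMAs per day × 3 days = 18 prompts per week (108 over 6 weeks).

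**Assumed inputs, because the document gives none:**

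- u = uptake of offered tasks
- r = share of brief EMAs answered
- p = share of answered EMAs that cross the trigger
- C = consolidating tasks offered per week

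**Formulas:**

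- Offered per week = C + 18 × r × p
- Completed per week = u × (C + 18 × r × p)

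**Halving the trigger rate, with u = 0.80 and r = 0.80:**

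| C | p = 0.40 | p = 0.20 | Fall |
|---|---|---|---|
| 0 (interactive only) | 0.8 × 5.76 = 4.61 | 0.8 × 2.88 = 2.30 | 50% |
| 3 | 0.8 × 8.76 = 7.01 | 0.8 × 5.88 = 4.70 | 33% |
| 7 | 0.8 × 12.76 = 10.21 | 0.8 × 9.88 = 7.90 | 23% |

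Uptake cancels from the percentage fall, so these falls hold at any constant u. Over r from 0.60 to 1.00 and C of 0, 3 or 7, the fall ranges from 19% to 50%.

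**Can the count order two participants wrongly?** Take r = 0.80. Participant A completes 90% of offers and triggers on 15% of EMAs. Participant B completes 50% and triggers on 60%.

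- C = 3: A = 0.9 × (3 + 2.16) = 4.64; B = 0.5 × (3 + 8.64) = 5.82. The less compliant participant scores higher.
- C = 7: A = 0.9 × 9.16 = 8.24; B = 0.5 × 15.64 = 7.82. The order is right.

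A reversal is therefore possible but depends on how many consolidating tasks are offered.

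**Completed divided by offered:** this equals u at every trigger rate tried (p from 0.60 to 0.10), so it no longer moves with symptoms.

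**What the ratio misses:** with C = 0, u = 0.80 and p = 0.40, the ratio is 0.80 whether 60% or 100% of EMAs are answered, while completed tasks are 3.46 and 5.76 per week. An unanswered prompt produces no offer and so drops out of the ratio. The EMA response rate has to be read with it.

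**The case against.** The strongest reply is that the article asks whether the intervention can be delivered, and that mean tasks completed per week is a fair description of how much practice took place. Consolidating tasks need no trigger, so they dilute any dependence on symptoms. EMI adherence is one of three parts of one criterion. The SAP, which is not shown, may add denominators and cut-offs.

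Much of this stands, and it rules out several stronger readings that a reader might infer:

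- **A fivefold swing in measured adherence.** At 60% uptake with every prompt answered, trigger rates of 50% and 10% give 18 × 0.5 × 0.6 = 5.4 and 18 × 0.1 × 0.6 = 1.08 tasks per week. That covers interactive tasks only. With 3 consolidating tasks per week the contrast is 7.2 against 2.9 (2.5-fold), and with 7 it is 9.6 against 5.3 (1.8-fold). The trigger rates are assumed throughout.
- **Adherence falls whenever the intervention works.** The target mechanism is the negative affect response to stress, not the number of unpleasant situations. A rating of stress below 0 still triggers a task in someone whose reactivity has improved, so any fall is partial and its size unknown.
- **Misclassified individuals or incomparable stages.** The article plans no ranking of participants and no comparison of adherence across stages 1a, 1b and 2, and it gives no trigger rates by stage.
- **A feasibility verdict decided by a cut-off on the count.** No such cut-off appears in the article.
- **Enhancing tasks left unmonitored.** They are outside this count, but the adherence checklist is said to cover all core components and its content is not shown.

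The objection does not remove the central point. The article does not leave the measure open: it spells out adherence to EMI tasks as a count. A cut-off on that count, wherever it was set, would inherit the dependence on how often tasks were triggered.

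**Conclusion.** The point holds in a limited form. The stated adherence measure combines uptake with the number of opportunities, and for interactive tasks that number depends on negative affect, momentary stress and response style. At constant uptake and EMA response, the interactive part would be expected to fall if negative affect or stress falls. Halving the trigger rate from 40% to 20% lowers the weekly count by about 50%, 33% or 23% with 0, 3 or 7 consolidating tasks offered per week at 80% EMA response. Apart from the 18 prompts per week, every input is an assumption, so these figures show the mechanism and a plausible range but do not predict what the trial will see. If the slash in the definition means that the two task types are reported separately, only the interactive count is affected. The documents do not show that the feasibility verdict would change.

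**What to change.** In the feasibility and adherence section:

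- Define adherence to interactive tasks as tasks completed divided by tasks offered, pooled over the 6 weeks.
- Report it separately from consolidating tasks (also completed divided by offered) and enhancing tasks (completed out of one per week).
- Show the number of interactive tasks offered and the brief-EMA response rate alongside.
- Keep the weekly count, labelled as a measure of exposure.
- Base any feasibility judgement on interactive-task adherence on the proportion together with the EMA response rate.

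The cost is a change of wording and a few extra descriptive columns. No new data are needed if the app logs each offer, which is an assumption to confirm with those who run it. The article places database lock after the last assessment, so the change can be recorded as a clarification before lock. The drawback is that the proportion is unstable for participants offered few interactive tasks. Pooling over the 6 weeks eases this, and showing the number offered makes it visible.

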### Candidate Mechanisms and Outcomes

#### Overview

After obtaining written informed consent, all eligible participants will be assessed on candidate mechanisms and outcomes before randomization (*baseline*, t_0_), after the 6-week intervention period (*postintervention*, t_1_) and after a 4-week follow-up period (*follow-up*, t_2_) by blinded assessors (Figure 1 and Multimedia Appendix 1). Research Electronic Data Capture (REDCap) [94], a secure, web-based software platform hosted at the CIMH servers, will be used for data collection.

#### Primary Candidate Mechanism

The primary candidate mechanism is a reduction in stress reactivity acquired by EMA from baseline to postintervention for the experimental condition compared with the control condition. EMA will include eight assessments per day, scheduled at random within set blocks of time, for 6 consecutive days at baseline, postintervention, and follow-up [43,95]. Momentary stress will be assessed using established and validated EMA measures of event-related stress, activity-related stress, and social stress (Textbox 2) [43,89]. We will compute a composite momentary stress measure (ie, the mean score of event-related, activity-related, and social stress) in line with the literature [52,96,97] and the EMIcompass pilot study [53]. Negative affect will be assessed using an established and validated EMA measure of negative affect [43]. Stress reactivity as the primary candidate mechanism will be computed in linear mixed models with composite momentary stress as the independent variable and negative affect as the outcome variable [43,89,95].

#### Secondary Candidate Mechanisms

Secondary candidate mechanisms (Multimedia Appendix 1 and Textbox 2) measured using EMA include threat anticipation, negative affective appraisals, emotional resilience to stress (operationalized as attenuated recovery in positive affect in response to minor stressors), and elevated stress reactivity (ie, increased negative affect) in response to event-related, activity-related, and social stress using subscale scores of the EMA stress measure. Threat anticipation will be additionally assessed using the Threat Anticipation Measure [62], asking participants to estimate the future likelihood of a list of negative, neutral, and positive events happening to themselves and other people [61-63]. Interpersonal sensitivity will be assessed using the Interpersonal Sensitivity Measure [98] in addition to EMA. Resilience will be measured using the Connor-Davidson Resilience Scale [99] and the Resilience Scale [100]. Furthermore, the Self-Compassion Scale [101], the Fife Facet Mindfulness Questionnaire [102], and the Cognitive Emotion Regulation Questionnaire [103] will be used to assess self-compassion and emotion regulation. In addition, we will assess physiological markers of stress reactivity using a sensor for ambulatory ECG and actigraphy (movisens ECGmove4) during the 6-day EMA at baseline, postintervention, and at follow-up.

#### Candidate Primary Outcome

The candidate primary outcome of this exploratory RCT is psychological distress measured using the well-validated Kessler Psychological Distress Scale [81]. The 10 items are rated on a 1 (never) to 5 (always) Likert scale focusing on psychological distress in the last month. Strong psychometric properties have been reported with a reliability of Cronbach α>.90 [81].

#### Candidate Secondary Outcomes

Secondary outcomes include primary (ie, psychotic, manic, anxiety, or depressive) symptoms and general psychopathology. These will be assessed using the following observer-rated measures: the Brief Psychiatric Rating Scale [104], including the Comprehensive Assessment of At-Risk Mental State [80], the Young Mania Rating Scale [105], the Hamilton Depression Rating Scale [85] and the Hamilton Anxiety Rating Scale [86]. On the basis of these measures, we will assess the transition to another clinical stage (according to a modified version of the clinical staging model by Hartmann et al [16]; see above). In addition, the following self-report measures will be used: the Brief Symptom Inventory [106], the Beck Depression Inventory [107], and the Prodromal Questionnaire [108]. Secondary outcomes further include quality of life measured using the WHO-Quality of Life assessment [109].

### Other Measures

Other study parameters will include basic sociodemographic characteristics, familial risk factors for psychopathology, and other parameters (including age, sex, alcohol or substance use, and childhood trauma [110]). The Client Service Receipt Inventory [87] will be used to record patients’ contacts with mental health services, monitor variation in the delivery of TAU, and model economic outcomes for a definitive trial. The Working Alliance Inventory [111,112] will be used to assess the relationship between practitioners and patients.

### Sample Size

A formal sample size calculation is not essential for this exploratory trial, which primarily seeks to establish feasibility, effects on candidate mechanisms, and initial signals of efficacy. In planning, we aimed to determine the sample size in such a way as to establish the feasibility of the methodology for conducting an RCT and delivering the EMIcompass intervention to youth with early mental health problems and initial signals of the efficacy of EMIcompass in reducing psychological distress as a candidate primary outcome (see Statistical Analysis Plan [113] for further detail) as a basis for a future definitive trial. For the latter, previous studies of third-wave CBT [72,114], including compassion-focused interventions [68,77], suggest that these types of interventions may yield clinically meaningful reductions in psychological distress of moderate to large effect size. This is consistent with the initial findings from an uncontrolled phase I pilot study [53]. However, even if the effect size for the main effect of condition on psychological distress (primary outcome) in this exploratory RCT is small, a power simulation in the R environment indicated that a sample size of N=80 participants (40/40, 50% experimental, 40/40, 50% control condition) would be sufficient to detect a small effect size of 0.3 across the postintervention 4-week follow-up with a power of 81% when testing at α=.05 for the effect of condition (experimental vs control condition) on psychological distress using linear mixed modeling, which will be tested using a Wald-type test of no difference between the two conditions across both time points against the two-sided alternative hypothesis that the conditions are, on average, different across the two follow-up time points (given the exploratory nature of this trial), while controlling for baseline psychological distress and group status. At the 4-week follow-up, we expect an attrition rate of 15%, resulting in a loss to follow-up of approximately 6 individuals per condition on average (Figure 1). Therefore, we will randomize a total of 92 participants at baseline, leaving 80 participants at follow-up to detect a small effect size of 0.3 at this time point. This sample size is also sufficient to test the criteria for establishing feasibility. Simulation studies on power and accuracy for multilevel mediation models with continuous variables [115] and our recently completed multilevel moderated mediation analysis of EMA data [42] suggest very little bias in parameter estimates with samples of this size (and 40 repeated measures, on average, per participant).

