### Statistical Analysis

The primary objective of this exploratory RCT is to establish the feasibility of the trial methodology and intervention delivery and initial signals of efficacy on the candidate primary outcome (ie, psychological distress) as a basis for a future definitive trial. In addition, this trial seeks to obtain parameter estimates (95% CI) for the effects on primary and secondary candidate mechanisms and candidate secondary outcomes. A detailed Statistical Analysis Plan [113] has been agreed with the DMEC and the TSC and has been preregistered and published on the Open Science Framework. It was registered while collecting the data before study completion and accessing the locked database. Descriptive statistics will be used, and CIs will be constructed as appropriate to compute basic sample characteristics and address the primary aim of establishing the feasibility of the trial methodology and intervention delivery based on the criteria described above and in further detail in the Statistical Analysis Plan using three categories (in line with a traffic light system): (1) feasibility fully established (green), (2) feasibility established, but study procedures need to be modified (yellow), and (3) feasibility not established (red) [113]. The analysis of candidate mechanisms and initial signals of efficacy has been described in detail in the Statistical Analysis Plan [113] and will be an intention-to-treat analysis or an available case analysis following intention-to-treat principles, with data from all participants entered into the analysis, including those who have low adherence to or who will drop out from the intervention. We will make every effort to assess all participants at postintervention and 4-week follow-up. Linear mixed modeling in Stata 16 will be used to compare candidate mechanisms and outcomes between experimental and control conditions at postintervention and 4-week follow-up. The primary candidate outcome of psychological distress measured at postintervention and 4-week follow-up will be entered as the dependent variable and psychological distress measured at baseline, group status (3-level factor), time (2-level factor), and condition (2-level factor) as independent variables. The main effect of condition on psychological distress will be parameterized so that it reflects the difference between the two conditions at the two follow-up time points (ie, postintervention and 4-week follow-up), which will be tested (at α=.05) by a Wald-type test with df=1, which tests the joint null hypothesis of no difference at both follow-up time points against the alternative hypothesis that there is, on average, a difference across the two follow-up time points. In addition, given the exploratory nature of this trial, with the main goal of establishing feasibility and obtaining parameter estimates for a future definitive RCT, 95% CI for the two time-specific contrasts of a time×condition interaction term will be inspected to obtain estimates for the differences across conditions at each of the two time points, with a time × condition interaction and a baseline psychological distress×time interaction added as independent variables to the previous model. Within-subject clustering of repeated measures (postintervention and 4-week follow-up) will be taken into account by including a level-2 random intercept and allowing the models’ level-1 residuals to be correlated with a completely unstructured error variance-covariance matrix. The model will be fitted using restricted maximum likelihood estimation. The analysis of secondary candidate outcomes and primary and secondary candidate mechanisms will, in principle, follow the same steps, focusing on 95% CIs (rather than P values at α<.05). Multilevel moderated mediation analysis of EMA data will be used to explore whether the effects of condition on primary (ie, psychotic, manic, anxiety, or depressive) symptoms are mediated via stress reactivity, threat anticipation, negative affective appraisals, and interpersonal sensitivity [42]. As participants will be randomly assigned to experimental and control conditions, no differences across conditions are expected in other study parameters (sociodemographic characteristics, alcohol or substance use, and childhood trauma). No statistical tests will be performed on these study parameters at baseline.

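### The 81% power stated for an effect of 0.3 averaged over both follow-ups does not carry over to the 4-week visit alone, and it holds only under high correlations that the article does not state

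*Protocol article*

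**What the plan says.** The Sample Size section of the protocol article reports a power simulation in R for "a sample size of N=80 participants (40/40, 50% experimental, 40/40, 50% control condition". It finds this number "sufficient to detect a small effect size of 0.3 across the postintervention 4-week follow-up with a power of 81% when testing at α=.05". The test is a Wald-type test of no difference "against the two-sided alternative hypothesis that the conditions are, on average, different across the two follow-up time points", "while controlling for baseline psychological distress and group status". The Statistical Analysis section gives the matching model: distress at the two follow-ups as outcome, with "psychological distress measured at baseline, group status (3-level factor), time (2-level factor), and condition (2-level factor) as independent variables".

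After allowing for attrition, the same section says that 92 will be randomized, "leaving 80 participants at follow-up to detect a small effect size of 0.3 at this time point". No separate power figure is given for that visit.

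The article does not state the correlation of baseline with follow-up distress, the correlation between the two follow-ups, or the SD in which 0.3 is expressed. It refers to the Statistical Analysis Plan for further detail.

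**The concern.** Two statements rest on one simulation, and that simulation is described only for the average of two visits. An average of two scores is less noisy than either score alone, so a sample size that suffices for the average need not suffice for one visit.

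The 81% also looks high for 40 per arm and an effect of 0.3. A plain two-group comparison at one visit, without baseline adjustment, has about 27% power. Everything between 27% and 81% must come from averaging and from covariate adjustment, and therefore from correlations that the reader cannot see.

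The section offers this as reassurance that even a small effect would be detected, and the trial is meant to inform a definitive one. A reader who relies on it could give a null distress result, above all one at 4 weeks, more weight against an effect of 0.3 than the design supports.

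**Working it through.** **Inputs from the article:** 40 per arm, effect 0.3, two-sided alpha 0.05, stated power 81%, adjustment for baseline and stage.

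**Assumptions:** 0.3 is in units of the total outcome SD (set to 1); the SD and the effect are the same at both visits; *r* is the correlation of baseline with each follow-up; *ρ* is the correlation between the follow-ups; stage explains nothing beyond baseline unless stated.

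**Formulas.** The variance of the estimated difference is (2/40) × v = 0.05 v, where

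- average of both visits: v = (1 + ρ)/2 − r²
- one visit: v = 1 − r²

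Power = Φ(0.3/√(0.05 v) − 1.96).

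**Step 1: the plan's own figure.** It cannot be reproduced, because r and ρ are not given, but it can be solved backwards. For 81% power, v = [0.3/(1.960 + 0.878)]²/0.05 = 0.2235. This is met by:

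- r = ρ = 0.83
- r = 0.79 with ρ = 0.70
- r = 0.76 with ρ = 0.60
- r = 0.74 with ρ = 0.55 (follow-ups independent given baseline, ρ = r²)

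**Step 2: carry-over to the 4-week visit, granting the 81%.** Subtracting the two formulas, the single-visit v exceeds the averaged v by (1 − ρ)/2. So v at 4 weeks = 0.2235 + (1 − ρ)/2, which equals 0.2235 only if ρ = 1.

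| ρ | v at 4 weeks | 0.3/√(0.05 v) | Power at 4 weeks |
|---|---|---|---|
| 0.55 | 0.4485 | 2.00 | 52% |
| 0.70 | 0.3735 | 2.20 | 59% |
| 0.83 | 0.3085 | 2.42 | 68% |
| 0.90 | 0.2735 | 2.57 | 73% |

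For 81% at the single visit, 1 − r² = 0.2235, so r = 0.88.

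**Step 3: how far the 81% depends on the correlations.** Power for the average, 40 per arm:

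| r = ρ | v | Power | Simulated (20,000 runs) |
|---|---|---|---|
| 0.5 | 0.500 | 47.5% | 47.6% |
| 0.6 | 0.440 | 52.5% | 52.7% |
| 0.7 | 0.360 | 60.9% | 60.6% |
| 0.8 | 0.260 | 74.9% | 74.2% |
| 0.83 | 0.226 | 80.6% | 79.9% |

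If the two vary separately within 0.5 to 0.7, power runs from 41% (r = 0.5, ρ = 0.7) to 75% (r = 0.7, ρ = 0.5).

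**Step 4: other readings of the inputs.**

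- Stage explaining a further 5% to 10% of variance (assumed): v = 0.500 − 0.05 = 0.45 gives 52% at r = ρ = 0.5, and v = 0.360 − 0.10 = 0.26 gives 75% at r = ρ = 0.7.
- All 92 seen at both visits (46 per arm): 53%, 58%, 67% and 81% at r = ρ = 0.5, 0.6, 0.7 and 0.8.
- 0.3 in residual-SD units: v = (1 + c)/2, with c the correlation of the residuals. If c is not negative, v is at least 0.5 and power at most 47.5%.

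**The case against.** The best defence is that the 81% comes from a simulation whose inputs an article may properly leave to the Statistical Analysis Plan. That stands. A reader might infer from Step 3 that the true power is 47% to 61% and that the 81% is an arithmetic error. The article does not support this. Those figures rest on assumed, equal correlations. Values of 0.74 to 0.83 are not excluded; the scale's stated reliability (above .90) is internal consistency, so it neither secures nor rules out such stability over 6 to 10 weeks. Stage may also explain some variance, which lowers the correlation needed. The 47% ceiling applies only if 0.3 was scaled to the residual SD, which the article does not say.

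A reader might also suspect a mix-up of total and per-arm numbers, since 80 per arm would give about 81% at a correlation near 0.6. That rests on one assumed correlation, and nothing in the article points to it.

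There is a case on the other side of the plausibility question. The low end, r = 0.74 with ρ = 0.55, has two scores 4 weeks apart agreeing less than baseline agrees with scores 6 to 10 weeks later, across an intervention. If ρ is at least as large as r, 81% needs r of at least 0.83. This is a reason to ask for the inputs, not proof that they are wrong.

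On the 4-week sentence, it can be said that no power figure is given there, that the phrase may only count who remains after attrition, and that the Statistical Analysis section treats time-specific contrasts as estimates with confidence intervals. The planned use is indeed modest, and the section itself calls a formal calculation not essential. Even so, the sentence claims that 0.3 can be detected at that visit, and the only support offered is a calculation for a different quantity.

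**Conclusion.** The carry-over to the 4-week visit does not hold on the article's own terms. Granting 81% for the average, power for 0.3 at 4 weeks is about 52% to 73% for follow-up correlations of 0.55 to 0.90. This needs only equal SDs and an equal effect at the two visits.

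The 81% for the average is conditional, neither confirmed nor refuted. It requires a baseline-to-follow-up correlation of about 0.74 to 0.83 with total-SD scaling and no contribution from stage. At assumed correlations of 0.5 to 0.7 it would be materially lower, by the amounts in Step 3.

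The consequence is limited. The trial is exploratory, feasibility is part of its primary objective, randomization of all 92 is complete, and no passage says that a null result would exclude 0.3. The matter is an over-favourable statement about what the trial can detect.

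**What to change.** 1. Withdraw the claim that 0.3 can be detected at the 4-week visit, or give that visit its own, lower power computed for a single-visit contrast.
2. Check the simulation for the SD that scales 0.3, the baseline-to-follow-up correlation, the between-follow-up correlation and the variance attributed to stage. State these, or point to where the Statistical Analysis Plan states them.
3. Restate the 81% as conditional on those inputs, and add power over a range, for example r = 0.5 to 0.8, which is about 47% to 75% with equal correlations and total-SD scaling. Label the range as a sensitivity display. The figures of 47% to 61% should not be printed as the delivered power, since they rest on assumed correlations.

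The cost is a check or rerun of an existing simulation and two rewritten sentences. No participants are added and the analysis does not change. The downside is a less favourable stated figure.
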